## Abstract

**Background:**

With the number of older adults in society rising, frailty becomes an increasingly prevalent health condition. Regular physical activity can prevent functional decline and reduce frailty symptoms. In particular, home-based exercise programs can be beneficial in reducing frailty of older adults and fall risk, and in improving associated physiological parameters. However, adherence to home-based exercise programs is generally low among older adults. Current developments in technology can assist in enlarging adherence to home-based exercise programs. This paper presents the rationale and design of a study evaluating the adherence to and effectiveness of an individually tailored, home-based physical activity program for frail older adults driven by mobility monitoring through a necklace-worn physical activity sensor and remote feedback using a tablet PC.

**Methods/design:**

Fifty transitionally frail community-dwelling older adults will join a 6-month home-based physical activity program in which exercises are provided in the form of exercise videos on a tablet PC and daily activity is monitored by means of a necklace-worn motion sensor. Participants exercise 5 times a week. Exercises are built up in levels and are individually tailored in consultation with a coach through weekly telephone contact.

**Discussion:**

The physical activity program driven by mobility monitoring through a necklace-worn sensor and remote feedback using a tablet PC is an innovative method for physical activity stimulation in frail older adults. We hypothesize that, if participants are sufficiently adherent, the program will result in higher daily physical activity and higher strength and balance assessed by physical tests compared to baseline. If adherence to and effectiveness of the program is considered sufficient, the next step would be to evaluate the effectiveness with a randomised controlled trial. The knowledge gained in this study can be used to develop and fine-tune the application of innovative technology in home-based exercise programs.

**Trial registration:**

Nederlands Trial Register (NTR); trial number 4265. The study was prospectively registered (registration date 14/11/2013).

## Background

As the number of older adults in our society rises
[1], health professionals, including physiotherapists, are increasingly confronted with frail older adults. Frailty is a multidimensional feature that has been defined and described in many different ways. A widely used definition is that of Fried
[2]: “Frailty is the state of vulnerability to stressors that is independent of any specific disease or disability but that is common in older people and predisposes them to various adverse health outcomes”. Frailty is an important predisposition for falls and associated adverse health conditions
[3]. Previous research indicates that regular physical activity has many beneficial effects on daily functioning, balance and strength, as well as other health-related factors in older adults
[4,5]. Exercise programs can potentially be helpful in reducing frailty of older adults and fall risk, and in improving associated physiological parameters, thus facilitating a longer independent life
[6]. Specifically, home-based physical activity programs can be considered promising in the promotion of a physically active lifestyle among frail older adults
[7]. Daily physical activity and adherence to home-based exercise programs is generally low among this group though
[8]. This compromises the effectiveness of home-based exercise programs.

Current developments in technology can assist physiotherapists in enlarging adherence to home-based exercise programs. The use of objective activity monitoring with wearable sensors can potentially be helpful in strategies aimed at increasing daily activity and adherence to home-based physical activity programs
[9]. Recent studies have shown the possibility to monitor mobility-related activities based on a thorax-worn motion sensor
[10] or motion sensors on the lower trunk
[11]. Such sensor-based approaches can be used to measure physical activity by detecting and monitoring different postures (i.e. lying, sitting, standing) and activities such as rising from a chair and walking. Motion sensing-based activity monitoring combined with information and communication technology (ICT) create the possibility to remotely monitor and influence daily physical activity behaviour in real life, instead of solely under laboratory circumstances or in a physiotherapy practice. Hence technology can assist in enlarging adherence by providing home-based exercise programs through gaining participant information and enabling remote contact with participants. The use of computers and tablets is steadily rising among older adults in the Netherlands
[12]. How such new technology can be used to optimally support exercise-based interventions tailored for older adults is not yet clear though.

We recently developed an innovative home-based physical activity intervention that is based on the use of a tablet PC in order to present a home-based exercise program and a necklace-worn motion sensor to continuously monitor mobility-related activities. The data monitoring is used for remote coaching of intervention participants. The current paper presents the design of a study that aims to evaluate the adherence to and effectiveness of our approach on independently living, transitionally frail older adults.

The primary research question is: What is the adherence to a home-based exercise program for use by older adults including exercise instructions from a tablet PC and monitoring by means of a necklace-worn motion sensor, as determined by adherence to the exercise program and wearing of the sensor?

Secondary research questions are: Does participation in the home-based exercise program (including use of the sensor and tablet) increase the daily amount of physical activity, measured both objectively and self-reportedly? Does participation in a home-based exercise program (including use of the sensor and tablet) improve functional performance?

## Methods

### Study design

This will be a prospective cohort study. Participants will join a 6-month home-based exercise program. Training and measurements will take place at participants’ homes. Study design and procedures are approved by the Medical Ethics Committee of the University Medical Center Groningen (UMCG). See Figure 
1 subsection for a flowchart of the study design.

**Figure 1 F1:**
[figure not shown]
Flow chart of the study design.

### Participants

Fifty subjects will be included. Inclusion criteria will be:

– Age 70–85 years.

– Transitional frailty as measured by the Groningen Frailty Indicator (GFI). The GFI is a screening instrument for level of frailty. Scores range from zero (not frail) to 15 (very frail). Older adults will be considered transitionally frail if they have a GFI score of 4 or 5. This GFI score indicates persons with only a minor elevated chance of loss of functionality and heightened disability
[13].

– Community dwelling or assisted living conditions.

– Ability to walk 10 m without support or using a cane or walker.

– Availability of a telephone.

– Ability to understand instructions regarding the use of the technology and execution of the exercise program.

Persons will be excluded based on conditions that hamper safe execution of the exercise program:

– Total hip or knee replacement in the past 6 months.

– Visual problems to a degree that makes it impossible for the subject to accurately read the questionnaires or walk around safely in his own home.

– Stroke within the last 6 months.

– Parkinson’s disease stage 4 or 5.

– Other neurological conditions that can impair daily functioning (e.g. dementia).

### Recruitment

Recruitment will be done by several means:

1) At information gatherings and when spreading information folders in neighbourhoods where many older people live.

2) Through healthcare organisations for older adults.

3) Recruitment in the participant pool of SamenOud. SamenOud is an UMCG-initiated project introducing a new healthcare model that combines all aspects of older-adult health care: living, well-being and care. SamenOud is running in the north-eastern part of the Dutch province of Groningen
[14].

### Intervention

All older adults participate in a home-based exercise program that consists of 3 months of home-based exercising with weekly telephone support from a coach and 3 months follow-up of exercising without coach contact. Participants exercise 5 days a week, starting with exercise bouts of 10 minutes which can progress up to 45 minutes. The program progresses in 18 levels. The first step-in level of the program consists of light and easy exercises, in order to accommodate for sedentary participants. Progression of difficulty and duration of exercises across levels elapses in small steps and in consultation with the coach. Participants are not obliged to finish all levels during the program.

The exercise program is based on the Otago Kitchen Table home-based exercise program, an individually tailored fall prevention program for muscle strengthening and balance-retraining exercises of increasing intensity used worldwide
[15,16]. The exercises are functional and closely related to daily activities (e.g. standing up from a chair).

From a behavioural point of view this program is based on insights from Social Cognitive theory
[17]. The program aims to enhance self-efficacy. Self-efficacy is defined as “the belief in one’s capabilities to organize and execute the courses of action required to manage prospective situations.”
[18]. It is hypothesised that by enhancing self-efficacy adherence to the program will improve. In order to enhance self-efficacy, motivational feedback is provided to the participant. The layout of the program as well as the provided feedback is based on the four main sources of efficacy information described by Bandura in the Social Learning theory. These sources include performance accomplishments, vicarious experience, social persuasion, and physiological and emotional states
[18]. The sources are used in four different strategies:

1) Exercises are presented by a role model in the instructional videos.

2) An encouraging message is provided after completing an exercise bout.

3) Automatic feedback on time spent “active” (standing and walking) is provided on a daily basis.

4) Weekly phone calls with the coach will be applied, addressing progression and motivational issues during the first three months.

Two devices are utilised during the program: a sensor to collect daily activity data and a tablet PC to provide exercise instructions and feedback.

#### Mobility monitoring

Daily mobility will be monitored by a necklace-worn motion sensor. The sensor is a miniature hybrid sensor that contains a 3D-MEMS accelerometer together with a barometric pressure sensor. Data is sampled at 50 Hz with a 4 mg resolution. A Micro-SD card will be used for data storage and exchange. The sensor weighs about 30 gr and measures about 55×25×10 mm. Measured sensor data is used to identify different activities, like standing, sitting, lying and walking
[10,19,20]. Daily activity level will be calculated based on these categories. Participants will wear the sensor during the daytime and connect it to the tablet PC at night for data upload and battery reloading.

#### Tablet PC

A tablet PC is provided as a user device to give exercise instructions and distant feedback. Functionality of the tablet PC is adjusted to independent older adult use, keeping menus and necessary interaction as simple as possible. Completion of the exercise bouts is notified through the tablet PC. Participants are able to choose their level of exercise, after which they are provided with a video showing the entire exercise bout being performed by an older adult, which they are asked to imitate. By means of this procedure they are guided through the entire exercise bout. The videos include a spoken explanation of the exercises while the exercises are being shown. After completing the video, a motivational message based on the rate of completion of the video appears on the screen. The tablet collects data on number of shown videos and the level of the videos shown. Feedback on daily activity level as registered by the sensor is provided by means of a graph that compares daily activity performance to one’s earlier performances as well as to a norm population.

### Outcome measures

Demographic characteristics (e.g. age, gender, family status and comorbidity) and information on experience with computers, tablets and smartphones will be collected at baseline. Also, written informed consent will be completed at baseline. In addition to the monitoring data, standardised measurements will be taken at baseline (T_0_), at 3 months (T_1_) and at 6 months (T_2_).

#### Primary outcome measure

*Adherence*: Adherence to the intervention will firstly be assessed based on adherence to the exercise program and wearing of the sensor. Adherence to the exercise program will be calculated based on completion of exercise bouts. Adherence to wearing the sensor will be calculated based on the number of days the sensor is worn and the successful collection of data. Adherence will be considered sufficient when adherence to the exercise program and to the wearing of the sensor exceeds 70%.

Additional information on factors that may influence adherence will be collected by means of a questionnaire. The user evaluation questionnaire is an adapted version of the SensAction-AAL subject evaluation form
[21]. The questionnaire contains questions about the perceived burden of the intervention, wearing of the sensor, and acceptability of the technology. Information will be collected at T_1_ and T_2_.

#### Secondary outcome measures

*Objective daily physical activity based on sensor data*: Baseline (T_0_) information on time spent “active” (standing and walking) will be collected while wearing the sensor for a week before starting the exercise program. A week of wearing will also be used as intermediate and follow-up information on daily activity at T_1_ and T_2_.

*Self-reported daily physical activity*: In addition to objective daily physical activity, self-reported daily physical activity will be measured by questionnaire at T_0_, T_1_ and T_2_. The Short Questionnaire to Assess Health-enhancing physical activity (SQUASH) gives an insight into habitual physical activity
[22]. The SQUASH consists of four domains: A) commuting activities, B) leisure-time activities, C) household activities, and D) activities at work and school. The questions within the four domains are prestructured into frequency, duration and intensity of an activity. Reproducibility and relative validity of the SQUASH for assessing physical activity have been evaluated
[22,23].

*Functional performance*: Functional performance is assessed by means of several clinical tests for physical functioning at T_0_, T_1_ and T_2_. First, subjects are requested to stand up from a chair at a self-selected pace (Sit-To-Stand; STS). STS is commonly used as a test to assess lower-limb strength and balance
[24,25]. Slower test scores are associated with higher fall risk in older adults
[26]. Subjects are instructed to sit still for several seconds, stand up from the chair at their preferred pace and then stand still for several seconds. The STS movement has good inter-rater and test-retest reliability in healthy older adults
[27]. The test is repeated three times if possible.

Second, the Timed Up-and-Go test (TUG) will be used to measure balance and functional mobility. The TUG is a widely used clinical test and is known to be associated with fall risk in older adults
[28,29]. The test protocol includes standing up from a chair, walking 3 m at a preferred speed, turning 180°, walking back and sitting down again. Intra-rater reliability ICC as well as inter-rater reliability ICC of the TUG are excellent
[30]. The test is deemed to be a valid measure of dynamic balance and functional control in older adults
[31]. This test will be repeated two times if possible.

Third, the Five-Times-Sit-to-Stand test (FTSS) will be used to indicate postural control and lower extremity strength. The FTSS has been associated with postural control, lower extremity strength and fall risk in older adults
[26]. Slower test scores have been related to more functional impairments in daily living among older adults
[32]. Subjects are instructed to stand up from a chair consecutively five times as fast as possible, preferably without using their hands for support. Test-retest reliability of the FTSS in community-dwelling older adults is adequate
[33,34]. The FTSS is deemed to be a valid measure of dynamic balance and functional ability in community-dwelling older adults
[31]. Inter-rater reliability is good to excellent
[34,35]. The test will be repeated twice if possible.

In addition, subjects follow a weekly functional performance self-assessment protocol independently while wearing the sensor. The protocol consists of one STS, one TUG and one FTSS test. Subjects are asked to shake their sensor five times before and after performing their self-assessment, to mark the self-assessment in their daily life data.

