### Data acquisition

Demographics collected by written questionnaire and information on adherence and personal circumstances collected during telephone contacts are manually entered into a database. Information on daily physical activity during the week of wearing and daily life data are collected by the worn sensor. These data are collected during the week before the home visits at T_0_, T_1_ and T_2._ Functional tests are performed during the home visits and by self-assessment; data from the functional tests are collected by using the sensor as well as by registration of duration using a stopwatch. For self-assessment, subjects note the date and time at which they perform the weekly self-assessment and shake the sensor five times before and after to mark the self-assessment in the daily life data. All sensor data are transmitted to a tablet by Bluetooth every night and then stored in a web-based interface. Stopwatch times are entered manually into the database.

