### Data analysis

Descriptive statistics will be used to describe the baseline and demographic characteristics as well as data on adherence. Changes in daily physical activity and performance on the functional performance tests at T_0_, T_1_ and T_2_ will be analysed by means of Repeated measures ANOVA. Subgroup analyses will be conducted taking into account the potential influence of age, gender, marital status, GFI and BMI. All data will be analysed with Matlab (version 2013a) and SPSS (version 20.0). A p-value lower than 0.05 will be considered statistically significant.

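### Change in sensor activity rests on one week per visit and a three-point ANOVA; a mixed model would keep participants with a missing week and use the follow-up data already held (minor)

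*Protocol article*

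**What the plan says.** All places are in the Protocol article.

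- **Window.** Under Secondary outcome measures, baseline active time (standing and walking) "will be collected while wearing the sensor for a week before starting the exercise program". For T1 and T2, "A week of wearing will also be used as intermediate and follow-up information on daily activity". Data acquisition fixes the timing: "These data are collected during the week before the home visits at" T0, T1 and T2.
- **Wear.** Background describes "a necklace-worn motion sensor to continuously monitor mobility-related activities". Mobility monitoring says "Participants will wear the sensor during the daytime and connect it to the tablet PC at night for data upload and battery reloading". Data acquisition adds "All sensor data are transmitted to a tablet by Bluetooth every night and then stored in a web-based interface". Study design gives the duration: "Participants will join a 6-month home-based exercise program".
- **Analysis.** Under Data analysis, changes in daily activity over the three time points "will be analysed by means of Repeated measures ANOVA".
- **Sizing.** Sample size calculation uses this outcome: a 15% increase, 80% power, significance level 0.05, 40 completers, and 50 enrolled after 20% dropout.
- **Other uses of the daily data.** These are the sensor-wear part of the primary outcome (days worn and data successfully collected, sufficient above 70%), daily feedback on active time, and the marked weekly self-assessments.

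**The concern.** Active time is recorded day by day for about six months, yet the change analysis takes one week at each follow-up point. Two costs follow.

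The first is completeness. A three-level repeated measures ANOVA in its classical form needs all three values. A participant with good data at T0 and T2 but a failed T1 week contributes nothing to that test. The 20% allowance is for dropout, and sensor adherence only just above 70% still counts as sufficient. Some loss of measurement weeks among completers is therefore compatible with a trial that succeeds on its primary outcome.

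The second is precision. One week can be atypical through illness, weather or family visits, and the neighbouring weeks that would reduce this noise are already stored.

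Both costs fall on the outcome that determined the number of participants.

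**Working it through.** **1. The plan's own figure.** The dropout step reproduces: 40 / (1 − 0.20) = 50. The 40 cannot be reproduced forwards, because no SD or within-person correlation is given. Solving backwards with a two-sided paired t-test (T0 against T2, n = 40, 80% power, alpha 0.05; two-sidedness is assumed) gives a standardised change of 0.454. The implied SD of change is 15 / 0.454 = 33.0% of baseline. The paired test stands in here for the planned three-point ANOVA.

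**2. Failed weeks.** Assume each required week fails independently with probability p; the article gives no rate. Complete cases over three weeks are 40 × (1 − p)³. If only the T0 week were irreplaceable, they would be 40 × (1 − p). Power is for the T0–T2 comparison at a standardised change of 0.454.

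| p | All three weeks needed | Power | Only T0 exposed | Power |
|---|---|---|---|---|
| 5% | 34.3 | 73% | 38 | 78% |
| 10% | 29.2 | 66% | 36 | 75% |
| 20% | 20.5 | 50% | 32 | 70% |

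In between lies a model that keeps the matched weeks but tolerates a missing T1. Participants with both T0 and T2 number 40 × (1 − p)² = 36.1, 32.4 or 25.6, with power of about 76%, 71% or 60%.

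**3. Ceiling on the precision gain.** Let f be the share of the change variance due to single-week error, split equally between T0 and follow-up, and let k be the number of independent follow-up weeks averaged. The variance ratio is (1 − f) + f(1 + 1/k)/2. Even with f = 1 and unlimited k it is 0.5, so the standard error cannot fall below √0.5 = 0.71 of its one-week value. With k = 4 and f = 25%, 50% or 75%, the factor is 0.95, 0.90 or 0.85.

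**4. Would a four-week mean at T2 be the better definition?** Assume a week-to-week within-person SD s of 10%, 15% or 20% of baseline. With independent weeks, Var(change) = 33.0² − s² × (1 − 1/4), which gives an SD of 31.9, 30.4 or 28.1. Two further assumptions are then varied:

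- *Trend.* A four-week window is centred 1.5 weeks earlier than its last week. If the 15% rise is linear over 26 weeks, the expected change becomes 15 × (26 − 1.5)/26 = 14.1%.
- *Correlation.* If the week-to-week deviations correlate at 0.5, the factor 1/4 becomes (1 + 3 × 0.5)/4 = 0.625.

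| Power with 40 completers (80% with one week) | s = 10% | s = 15% | s = 20% |
|---|---|---|---|
| Independent weeks, stable activity | 83% | 86% | 91% |
| Independent weeks, linear rise | 78% | 82% | 87% |
| Correlation 0.5, stable activity | 81% | 83% | 85% |
| Correlation 0.5, linear rise | 77% | 78% | 81% |

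The gain from a longer window is not robust, and in some settings power falls below the starting 80%.

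**The case against.** The strongest reply is that one week at each time point is a matched design. Baseline can only be a week before the programme starts, and all three weeks precede a home visit. Any extra effort because a visit is near, if similar in size each time, cancels from the change. A four-week follow-up mean would carry only about a quarter of that effort against a baseline carrying all of it. It would also blur the 3- and 6-month points while activity may be trending. This stands. The window is not an error or a contradiction, and replacing it by four-week means is not a clear improvement.

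A reader might infer that the remaining sensor data are discarded. The article does not support that: they feed sensor-wear adherence, daily feedback and self-assessment, and nothing says they will not be analysed further. What remains true is that the stated change analysis does not use them.

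A reader might also infer that the plan excludes anyone whose week fails. No such rule is stated. The loss follows from the classical form of the named method, and rules for invalid or substitute weeks may sit in a fuller document that is not shown. The point therefore concerns the choice of ANOVA, which the article does state, and not the absence of a missing-data rule.

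One sentence in Data acquisition, which places the collection of daily life data in the week before the visits, could be read against continuous wear. Nightly upload, daily feedback, adherence counted in days worn and weekly marked self-assessments all favour daily wear.

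Finally, this is a secondary outcome of an uncontrolled study whose primary question is adherence. That limits the severity, although the sample size still rests on it.

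**Conclusion.** The point holds as a minor one. The article fixes a three-point repeated measures ANOVA on one week per visit for the outcome that sized the study, while daily data on the same variable accumulate throughout follow-up. A mixed model would keep participants who miss a time point and could use those data.

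The benefit is small to moderate and rests wholly on assumptions, because the documents give neither a variance nor a week-failure rate. With assumed failure of 5% to 20% per required week, independent across weeks, complete cases fall from 40 to about 34 to 20. Making the follow-up weeks replaceable would limit this to 38 to 32. The precision gain is capped at a 29% smaller standard error, and a failed T0 week cannot be replaced by later data. The 40 completers do not show whether single weeks are precise enough, since the 33% SD is only what that number implies.

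**What to change.** 1. Keep the matched pre-visit week as the definition of activity at T0, T1 and T2.
2. Replace the repeated measures ANOVA for this outcome by a linear mixed model with time point as a fixed effect, which keeps participants with a missing time point.
3. Add a mixed model on all valid weekly means (the baseline week plus the follow-up weeks), with time modelled explicitly, and estimate change at 3 and 6 months.
4. Do not make four-week means the main definition of T1 and T2.

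**Cost.** The change is to analysis wording and code only, with no new data collection. A time trend and a within-person correlation structure must be specified in advance. Estimates with missing weeks rely on the loss being explicable by the observed data (missing at random), which should be stated.
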